### Blinding

Participants and intervention delivery facilitators could not be blinded to group allocation. Evaluators conducting the clinical assessments were blinded to group allocation.

### Interventions

#### Overview

All participants that fulfil inclusion criteria were invited to participate. Information about objectives, duration, procedures, and voluntariness was given to patients and informed consent was obtained. None of the procedures of the study started before the informed consent had been signed by the participants.

#### Control Group

The patients allocated in the control group, after the baseline assessment, received general written recommendations on the aforementioned major areas (physical activities, sleep, cognitive, and nutrition; social support and stress management for caregivers). At the end of the study period, patients performed end-of-study evaluations.

#### Intervention Group

The patients recruited and assigned to the experimental group received specific instruction in using the project platform, but without any specific program concerning the activities.

Specifically, patients, after the baseline assessment, received the instrumental setup and indications on its functionalities. Patients were instructed about the use of the Fitbit, the PC4L app, and the cognitive games on a tablet or computer. Patients were also provided with manuals.

Specifically, according to the study approach detailed by Biehl et al [9], the patients were instructed to complete the following questionnaires in the app during the first week and during the last week of the study period: the 10-item Eating Assessment Tool (EAT10) [13] for evaluation of dysphagia; the Edmonton Symptom Assessment System (ESAS) [14] and the Patient Global Impression (PGI)—Severity [15] for evaluation of symptoms; and the International Physical Activity Questionnaire (IPAQ) [16] for evaluation of physical activity. In addition, during the last week of using the app, patients were requested to complete the SUS [17], via the app, for evaluation of usability.

The platform was installed in each scenario with the assistance of the project research staff (ie, bioengineers).

A total of 2 versions of PC4L systems were installed: while the cloud-based system (which only required a smartphone and a wearable sensor) was used in all scenarios, a fully equipped version was implemented only in the rehabilitation scenario.

The patients received the same directions in all 3 scenarios.

At the end of the study period, patients performed end-of-study evaluations and returned the instrumental setup.

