### Study Assessments

In-person assessments took place at baseline and at the end of the study (3 months follow-up or at discharge from the rehabilitation program).

Specifically, the sample characterization and clinical evaluation of the participants (both experimental and control group patients) were performed at baseline. The clinical evaluation with specific tests and scales was repeated at the end of the study.

At the beginning and at the end of the study, all patients were assessed on quality of life through a specific scale (EQ-5D-3L).

Only for patients assigned to the intervention group, their experience with the PC4L platform was assessed in terms of usability at the end of the experimental period.

Figure 3 and the “Data Collection and Analysis” section report specific outcomes that will be used.

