### Statistical Analysis

Descriptive analysis will be performed for all variables to characterize the sample. For continuous variables, mean, SD, median, and range values will be calculated. For categorical variables, absolute and relative frequencies will be used to describe the data [29-31].

Normality will be studied using the Kolmogorov-Smirnov and Shapiro-Wilk tests. The effect of using the PC4L system will be analyzed by applying the paired-sample *t* test (2-tailed) and the Wilcoxon signed rank test to each variable (statistical significance will be set at P<.05).

The Pearson and Spearman correlation tests will be used to validate the PC4L systems metrics (statistical significance will be set at P<.05).

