## Discussion

PC4L recognizes that today in health care an integrated care process should be adopted for harmonizing health models with social services from a holistic perspective [35]. Therefore, the project intends to develop and test a technology-based, integrated, scalable, and interactive care platform by involving patients with neurodegenerative diseases, such as PD and dementias. The principal aims of this project are to improve the quality of life of patients and to enable active living and better disease management. These aims will be achieved through large-scale assessments across Europe (in 5 countries and 6 end user organizations), with the final scope to validate the reliability of the overall system in a real-life context.

Eventually, the main advantage of the PC4L project is to propose a system that can be easily adapted to the reality of various chronic diseases, care institutions, and end user needs, thus benefiting all actors involved.

To assess the impact on quality of life and usability, we decided to adopt a randomized controlled trial model because it minimizes selection bias and allows reaching an adequate sample size to achieve power.

In the context of improved technologies and digitalization strategies, the use of wearable sensors and smartphone apps has the advantage of providing objective, longitudinal, and precise information about the status of the patients in their own home environment, as highlighted by Klucken et al [36], especially in cases of neurodegenerative diseases.

Based on the extensive literature on the benefit of physical activity in neurodegenerative diseases [37-46], we expect an improvement in quality of life. This is also facilitated by the early detection of signs and symptoms (eg, falls) through proactive monitoring.

Moreover, in terms of digital health, the inclusion of participants is a crucial part [47]. Based on our recent work, we considered that the ICT-integrated care platform should not promise functionalities that are too complex for too many users [11]. Instead, we focused on selection and restriction to fewer but essential aspects. Users and other stakeholders have in fact been involved in these decisions by being considered active actors from the early stages of the project. Notably, the clinical study here described is conducted in 3 different real-life scenarios, providing relevant information on the everyday life of the patients.

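### EAT10, ESAS, PGI-Severity and IPAQ are collected only in the PC4L arm and only after hand-over, yet nothing keeps their change out of the tests of the system's effect, and no activity measure covers both arms

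*Protocol article*

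**What the plan says.** The Intervention Group section sets the order of events: "patients, after the baseline assessment, received the instrumental setup and indications on its functionalities". It then names EAT10 for dysphagia, ESAS and PGI-Severity for symptoms, and "the International Physical Activity Questionnaire (IPAQ) [16] for evaluation of physical activity", and states that "the patients were instructed to complete the following questionnaires in the app during the first week and during the last week of the study period". In the last week, patients also complete the SUS in the app.

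The Control Group section says that these patients "received general written recommendations on the aforementioned major areas" (physical activity is one of the areas), and then: "At the end of the study period, patients performed end-of-study evaluations". It mentions no app and none of the four questionnaires.

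For assessments common to both arms, the Study Assessments section says that the sample characterization and "clinical evaluation of the participants (both experimental and control group patients) were performed at baseline", with the clinical evaluation repeated at the end and EQ-5D-3L taken from all patients at both times. The scales are listed under Clinical Assessment and Quality of Life Assessment.

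The Statistical Analysis section reads: "The effect of using the PC4L system will be analyzed by applying the paired-sample" t test and the Wilcoxon signed rank test, to all variables without exception. The Discussion gives the expected mechanism: "Based on the extensive literature on the benefit of physical activity in neurodegenerative diseases [37-46], we expect an improvement in quality of life".

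**The concern.** A change score from one arm cannot separate the system from anything else that moves patients over the same weeks, such as disease progression, a concurrent rehabilitation programme or regression to the mean. Here the first value is also taken while the patient already has the device, so even the within-arm change does not start from an untreated state. No choice of test repairs this later, because the control values do not exist.

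Two things are at stake. If the Statistical Analysis section is followed as worded, the first-to-last-week change in symptoms, swallowing or activity can be tested and reported as an effect of PC4L. And the trial would have no controlled evidence on physical activity, the route by which its authors expect quality of life to improve, although the controls were themselves given written advice on activity.

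**Working it through.** The plan states no figure for this point, so the main check is to set its sections side by side. The sample size (558, or 279 per arm) is not in dispute here; 279 is used only as the size of the PC4L arm.

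**1. Who completes the four forms.** They are named only under Intervention Group and are filled in through the app. Controls have no app. As described, 0 of 279 controls have any of the four scores.

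**2. When the first value is taken.** The order is baseline assessment, then hand-over and instruction, then in-app forms during week 1. The in-person baseline visit precedes hand-over but does not include these forms.

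**3. What both arms have.** Clinical Assessment lists MDS-UPDRS, CDRS, FES-I, PSQI, STAI, Barthel Index, PACIC, SAPS and CIRS-G, plus the presence of festination, dysphasia, wandering and unplanned use of medical resources. Quality of Life Assessment adds EQ-5D-3L. None of the four forms is there. The abbreviations in the Figure 3 legend do not include them either.

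**4. Physical activity.** IPAQ is confined to the PC4L arm. The wristband and phone metrics in Table 1 come from the PC4L system, so they too exist only in that arm. The Barthel Index and MDS-UPDRS rate function and disease signs, not amount of activity. No activity measure is described for both arms.

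**5. Which analysis applies.** The paired tests are described as showing the effect of the system and are not restricted to two-arm variables or to listed outcomes. A first-week and last-week pair fits that test directly.

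**6. Size of the risk.** Let δ be the mean change that has nothing to do with PC4L, divided by the SD of the change. For a two-sided paired test at 0.05 with n patients and no true system effect, by normal approximation:

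P(P<.05) = Φ(δ√n − 1.96) + Φ(−δ√n − 1.96)

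With n = 279, √n = 16.70. The column for n = 200 is an assumed case of incomplete in-app completion (√n = 14.14).

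| δ (assumed) | δ√279 | P<.05, n = 279 | P<.05, n = 200 |
|---|---|---|---|
| 0 | 0 | 5% | 5% |
| 0.05 | 0.84 | 13% | 11% |
| 0.10 | 1.67 | 39% | 29% |
| 0.15 | 2.51 | 71% | 56% |
| 0.20 | 3.34 | 92% | 81% |

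Example for δ = 0.10, n = 279: Φ(1.67 − 1.96) = Φ(−0.29) ≈ 0.386, and the second term is negligible. In a comparison of change between randomized arms, drift common to both arms cancels and the rate returns to 5%.

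**The case against.** The strongest reply is that these forms are not outcomes. The Aims section lists one primary and five secondary outcomes and names none of the four. The PC4L Mobile App and Decision Support System sections present app questionnaires as a component of the app and an input to its recommendations, and inputs to an intervention are naturally collected only where it is given. This stands. A reader might infer that the trial has lost controlled outcomes or that its primary comparison is damaged. The article does not support that: EQ-5D-3L is taken in both arms at both visits, with the PC4L arm's baseline before hand-over, and related domains (motor and nonmotor signs of PD, sleep, anxiety, fear of falling, daily function) are rated in both arms.

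It can also be said that the Discussion sentence is rationale and not a mediation hypothesis, and that no stated objective compares activity between arms. That is correct, and it makes the missing activity measure a gap in interpretation, not a broken objective. Reliance on paired tests is also a wider weakness that affects two-arm variables. The difference is that two-arm variables can still be reanalysed between arms, and these four cannot.

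Four further inferences are tempting but not established:
- The article does not say when notifications began, so the first score cannot be said to follow them.
- A shift in the week-1 score from wearing the device is possible, but its size cannot be derived.
- The order of the last-week forms and the end-of-study EQ-5D-3L is not given, so an influence of one on the other is conjecture.
- The rehabilitation share, 204/558 = 36.6%, counts both arms. The number of PC4L patients in rehabilitation is not stated.

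Finally, this is a condensed article, Figure 3 is not shown, and the full protocol may define the role of these forms. The article does describe them as evaluating dysphagia, symptoms and activity, in the same paragraph as the SUS, which is a listed outcome, and nowhere marks them as inputs only.

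**Conclusion.** The point holds in a limited form. As described, the in-app EAT10, ESAS, PGI-Severity and IPAQ scores have no concurrent control and no pre-system value, and the wording of the Statistical Analysis section would let their change be reported as an effect of PC4L. In addition, no physical activity measure is collected in both arms, although activity is the stated reason for expecting better quality of life.

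If the paired tests were applied to these scores, unrelated drift of 0.10 to 0.20 SD of the change would give P<.05 in about 39% to 92% of cases with 279 patients. This rests on assumed drift, complete data, no true system effect and a normal approximation; the document gives no drift or SD for any of the four forms. It concerns supportive inference only. The primary comparison and the listed secondary outcomes are not affected by it.

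**What to change.** **By design.** Give at least IPAQ, and any of the other three that is meant to measure an effect, to both arms at the existing in-person baseline visit, before the system is handed over, and again at the end visit. Compare the arms. At the end visit have EQ-5D-3L completed first in both arms, so that the order of forms is fixed and equal.

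**In the analysis text.** State that the in-app scores are descriptive platform inputs and are excluded from the tests of the system's effect.

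**For the present trial.** The article reports that enrollment ended in February 2023 and that participation lasts at most 3 months, so a pre-system baseline probably cannot now be collected. Where control data cannot be obtained, report the in-app scores descriptively and make no claim of activity or symptom benefit from them.

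**Cost.** No extra visit is needed. The design change adds some questionnaire time at two visits for patients aged 65 or older who already complete a long battery, which is a reason to limit it to IPAQ unless the others are needed. The text change costs a sentence or two.

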### Study Assessments

In-person assessments took place at baseline and at the end of the study (3 months follow-up or at discharge from the rehabilitation program).

Specifically, the sample characterization and clinical evaluation of the participants (both experimental and control group patients) were performed at baseline. The clinical evaluation with specific tests and scales was repeated at the end of the study.

At the beginning and at the end of the study, all patients were assessed on quality of life through a specific scale (EQ-5D-3L).

Only for patients assigned to the intervention group, their experience with the PC4L platform was assessed in terms of usability at the end of the experimental period.

Figure 3 and the “Data Collection and Analysis” section report specific outcomes that will be used.

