### Aims

This study represents the third, and last, phase (pilot 3) of large-scale pilots aiming to gradually co-design and iteratively test the PC4L integrated platform and modules.

While pilot phases 1 and 2 focused on technical feasibility and patients’ satisfaction, this protocol focuses on the following objectives:

To assess the impact of using the PC4L platform on patients’ quality of lifeTo compare the metrics generated by the PC4L platform in real-life conditions with the clinical outcome measuresTo evaluate the feasibility and safety of measuring disease progression and patient health status through the global functioning of the PC4L systemTo assess and compare the feasibility and usability of 2 different versions of the PC4L system (fully equipped version vs cloud-based solution)To increase patients’ safety and empowerment

As the primary outcome, the study will provide:

The difference in quality of life between groups (experimental vs control group), measured by the EQ-5D-3L scale at the end of the study

The following secondary outcomes will also be acquired:

The correlation coefficient of the PC4L platform metrics (eg, steps and physical activity levels, sleep, number of falls, cognitive scores) with the clinical outcome measures (eg, motor clinical evaluation, sleep questionnaire, Falls Efficacy Scale-International [FES-I], cognitive evaluations) measured at baseline, end of the study, and the values of change from baselineSystem usability assessment, measured through the System Usability Scale (SUS), at the end of the studyUsers’ satisfaction with the PC4L system, measured through a 5-point Likert Scale, the mHealth User Satisfaction Questionnaire, and the participants’ answers to open questions, at the end of the studyChanges in patients’ satisfaction and empowerment, measured by the Patient Assessment of Chronic Illness Care (PACIC) and the Short Assessment of Patient Satisfaction (SAPS) scales, respectively, at baseline and at the end of the studyChange in patients’ use of medical resources (number of admissions and number of days spent in health institutions) in the last month, measured at baseline and at the end of the study

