### Study Design

A prospective multicenter clinical study is conducted in 5 European countries: Germany, Italy, Portugal, Romania, and Spain (also including 6 pilot centers).

The pilot sites are (1) Asociacion Parkinson Madrid (APM), Madrid (Spain); (2) Casa di Cura del Policlinico (CCP), Milano (Italy); (3) Campus Neurológico Sénior (CNS), Lisbon (Portugal); (4) University and Emergency Hospital of Bucharest (UHB), Bucharest (Romania); (5) University of Medicine and Pharmacy (UMF), Bucharest (Romania); and (6) Wohlfahrtswerk für Baden-Württemberg (WBW), Stuttgart (Germany).

There are also 3 different scenarios: (1) rehabilitation center (inpatients and outpatients); (2) day care centers; and (3) home set (ie, patients’ home).

The duration per patient, at home and in the day care center, will be up to 3 months. Participants in the rehabilitation center participated during the period of their stay in the center (not exceeding the 3 months).

A specific route diagram is presented in Figure 2 in accordance with the CONSORT (Consolidated Standards of Reporting Trials) guidelines. The protocol of this study was developed in accordance with the SPIRIT (Standard Protocol Items: Recommendations for Interventional Trials) guidelines (Figure 3) [12]. The schedule of enrollment, interventions, and assessments is presented in Figure 3.

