### Recruitment

Patients with PD and other parkinsonian syndromes, AD, or ODs were invited to participate from the clinical centers involved in the study. Each participant organization was assigned to recruit a number of participants related to their skills, experience, number of researchers involved, and access to users (Table 2).

**Table 2 table2:** Distribution of participants per clinical center and scenario.

Scenario/clinical center	Rehabilitation (n=204), n	Day care (n=82), n	Home (n=272), n	Total (N=558), n
APM^a^	80	N/A^b^	26	106
CCP^c^	63	N/A	62	125
CNS^d^	46	N/A	86	132
UHB^e^	15	N/A	15	30
UMF^f^	N/A	30	30	60
WBW^g^	N/A	52	53	105

^a^APM: Asociacion Parkinson Madrid.

^b^N/A: not applicable.

^c^CCP: Casa di Cura del Policlinico.

^d^CNS: Campus Neurológico Sénior.

^e^UHB: University and Emergency Hospital of Bucharest.

^f^UMF: University of Medicine and Pharmacy.

^g^WBW: Wohlfahrtswerk für Baden-Württemberg.

To reach the planned number of recruits, many strategies were implemented: participants were contacted through online webinars; through brochures placed in specific centers such as pharmacies, leisure centers, and medical offices; and through patients’ associations. Further, regular updates were posted via online newsletters on different websites, such as the PC4L website and end users organizations’ websites. In addition, information about the PC4L pilot 3 study was shared during national and international conferences. Recruitment was also promoted in a collaborative way thanks to partners from other European projects. Finally, participants were recruited in person when accessing the medical facilities and via phone contact or emails after searching local databases.

Patients who discontinue the study participation because of medical conditions (ie, infections, falls, medical emergencies) or unwilling to participate any longer for other reasons (ie, difficulty with technology, loss of interest) will be considered dropouts.

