Regarding the home scenario, the primary advantage of implementing this scenario is the ability to monitor patients at home, measuring their general health condition, asking about their perceived state, and detecting their symptoms (eg, gait disturbances or falls). The acquisition of these data will enrich patients’ perception of their own condition and will allow the comparison between their insight and the clinical and instrumental data. Health professionals, from their perspective, can take advantage of all these data by adapting the prescribed therapy in a highly personalized manner. Thus, patient-doctor communication will be improved, facilitating patients’ engagement with their own health care process.

Central to the study is also the implementation of the PC4L solution in the rehabilitation centers, as such controlled environments involve patients in different kinds of activities, under the supervision of a multidisciplinary team. Here, patients perform personalized treatments in dedicated rooms, such as motor training and exercises connected to ADL, as well as cognitive exercises to improve memory and attention. The main advantages of PC4L in this scenario are (1) the possibility to provide objective information to professionals to study the evolution, treatment personalization, and rehabilitation suggestions; (2) to check the communication between professionals, patients, and caregivers, especially exercise recommendations based on the evolution of patient’s movement skills; and (3) to design a decision support tool taking into account the patient’s personal and health condition.

Finally, in the third scenario of day care centers, patients perform activities connected to ADL like at home, but under the supervision of professionals (day care center workers). Additionally, the participation of caregivers in this scenario can support the patients. The benefits are to check the communication between professionals and the caregiver, who does not live in the same house with the patient, and to monitor the patient’s evolution.

In this pilot study, as already reported by Espay et al [48], low digital skills could be a limitation to the appropriate use of the PC4L solution and, therefore, the correct monitoring of the participants. The consortium mitigated this risk by adopting simplified age-appropriate questionnaires and tools.

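### The single primary EQ-5D-3L comparison is taken at 3 months for home and day-care patients but at discharge for the 204 rehabilitation patients (37%), so the pooled result is not a 3-month effect

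*Protocol article*

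**What the plan says.** The Aims section of the protocol article names one primary outcome: "The difference in quality of life between groups (experimental vs control group), measured by the EQ-5D-3L scale at the end of the study".

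Study Assessments ties the questionnaire to the two clinic visits ("At the beginning and at the end of the study, all patients were assessed on quality of life through a specific scale (EQ-5D-3L") and defines when those visits happen: "In-person assessments took place at baseline and at the end of the study (3 months follow-up or at discharge from the rehabilitation program".

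Study Design gives the matching participation periods. For two scenarios: "The duration per patient, at home and in the day care center, will be up to 3 months". For the third: "Participants in the rehabilitation center participated during the period of their stay in the center (not exceeding the 3 months". No minimum stay is given, and this third scenario covers both kinds of patient: "rehabilitation center (inpatients and outpatients".

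Table 2 in Recruitment gives the size of the group under the discharge rule: "Rehabilitation (n=204), n", out of 558.

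The Methods paragraph of the abstract gives the duration as 3 months, without the rehabilitation exception. The Statistical Analysis section names paired t tests and Wilcoxon signed rank tests, which carry no term for scenario or for time in the study.

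**The concern.** A between-arm difference is normally tied to a stated follow-up time. Here one number combines an outcome set by the calendar with one set by an event, and the event may come well before 3 months. Three things follow.

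- **Interpretation.** The pooled estimate averages over different lengths of exposure. A reader of the abstract would take it as the effect of 3 months of use.
- **Dilution.** If a shorter stay produces a smaller effect, the pooled effect falls below the 6 points behind the sample size.
- **Timing by arm.** Discharge happens after randomisation. The Discussion expects the platform to offer rehabilitation professionals "the possibility to provide objective information to professionals to study the evolution, treatment personalization, and rehabilitation suggestions", and days spent in health institutions are part of a secondary outcome. An effect of allocation on length of stay is therefore conceivable. If it occurred, the two rehabilitation arms would be measured at different times. Blinded evaluators protect the rating but not its date.

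**Working it through.** **1. Share under each rule (Table 2).**
- Rehabilitation: 80 + 63 + 46 + 15 = 204
- Day care: 30 + 52 = 82
- Home: 26 + 62 + 86 + 15 + 30 + 53 = 272
- Total: 204 + 82 + 272 = 558. Share under the discharge rule: 204/558 = 36.6%. Remainder: 354/558 = 63.4%.

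**2. The plan's own sample size.** Inputs from Sample Size: 279 per group, 95% power, 6 points (10%), with 5.23 points cited as the minimal clinically important difference. Inputs from Statistical Analysis: P<.05, 2-tailed. No SD is given, so 558 can be neither confirmed nor refuted. The SD it implies, by normal approximation, is

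SD = δ × √(n/2) / (1.960 + 1.645)

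- δ = 6: 6 × √139.5 / 3.605 = 6 × 11.81 / 3.605 = 19.7
- δ = 5.23: 5.23 × 11.81 / 3.605 = 17.1

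**3. Illustration of dilution.** Assume that the effect at discharge is a fraction f of the 3-month effect, that f applies to all 204 rehabilitation patients, and that the SD is 19.7.

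Pooled effect = 6 × (0.634 + 0.366 f)

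Power = Φ(pooled effect × √139.5 / 19.7 − 1.96)

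| f | Pooled effect (points) | Power |
|---|---|---|
| 1 | 6.00 | 95.0% |
| 0.75 | 5.45 | 90.6% |
| 0.50 | 4.90 | 83.8% |
| 0.25 | 4.35 | 74.4% |
| 0 | 3.81 | 62.8% |

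Starting from 5.23 points and SD 17.1 gives the same powers, because the ratio of difference to SD is unchanged. The pooled effects are then 4.75, 4.27 and 3.80 for f = 0.75, 0.50 and 0.25.

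**4. Where the pooled effect crosses the plan's threshold.** Starting from 6 points, it drops below 5.23 when f < (5.23/6 − 0.634)/0.366 = 0.65.

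**5. A factor that may work the other way.** The Intervention Group section restricts the fully equipped version to rehabilitation, and the section on system versions puts 70 of 279 intervention patients on it. If allocation was balanced within rehabilitation (an assumption), about 204/2 = 102 intervention patients are there, so roughly 70/102 = 69% of them had the fuller system. A stronger intervention could offset shorter use, so f may not be below 1 at all.

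**The case against.** The strongest reply is that nothing is hidden. The body of the article states both rules, and the visit can be read as the end of participation in each setting, which is when equipment is returned. Randomisation makes expected length of stay comparable between arms at the outset. Scenario terms and tables of follow-up time are ordinary content for an analysis plan that is not shown. Much of this stands: the end of participation is a legitimate endpoint, and the article does not say that scenarios will be pooled without adjustment. It does not remove the mixture in the single primary difference, nor does it make that difference a 3-month result.

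Several stronger readings are tempting and go beyond the document.

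- *Unblinded staff who see platform output set the assessment date, so the comparison is biased.* The article does not say who decides discharge. It calls participants and delivery facilitators unblinded, and its remarks on the platform's value in rehabilitation do not describe its use for timing discharge.
- *The other 354 patients have a fixed time point.* Study Assessments says 3 months, but Study Design sets 3 months as an upper limit for them too.
- *37% of patients have short follow-up.* That is the share under the discharge rule. Some of them, outpatients included, may stay close to 3 months.
- *The trial is underpowered.* The SD is back-solved and the fractions are hypothetical, so the table shows sensitivity and nothing more.

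**Conclusion.** The point holds as one of interpretation and analysis. The primary comparison uses two definitions of its final visit. The discharge rule covers 204 of 558 patients (36.6%), with a cap and no minimum, so the pooled estimate mixes exposure lengths and should not be called a 3-month effect.

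How much this matters numerically is unknown, because stay length is not given. Under the assumptions shown (SD about 19.7, a smaller effect at discharge), power would be 91% to 74% for f from 0.75 to 0.25. The fully equipped system could act in the opposite direction.

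Bias from arm-dependent discharge is a possibility to check against the assessment dates. It is not a demonstrated fault.

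**What to change.** - Include scenario, which is known at baseline, as a covariate in the between-arm analysis of the primary outcome.
- Report the effect in each scenario with a treatment-by-scenario interaction, and label the interaction as low-powered.
- Tabulate time from randomisation to the final assessment by arm within scenario. This directly checks whether timing differs by arm.
- Describe the pooled result as measured at the end of participation (3 months or discharge), and limit any 3-month statement to the home and day-care patients.

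Time in study belongs in the table and not among the covariates, because it arises after randomisation.

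Adding a 3-month telephone or postal EQ-5D-3L for rehabilitation patients is not advised. Equipment goes back at the end of their study period, so a later call would measure them after the system had been removed. Enrolment also closed in February 2023.

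The cost is a little extra analysis, using scenario and assessment dates that should already be on file, and scenario-specific estimates that will be imprecise, most of all for the 82 day-care patients.
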